**Laboratory facilities:**

[name] has a well-equipped plethysmography laboratory adjacent to clinical and education areas within the Endocrinology Suite in the Echelon Centre, a facility jointly leased by Vancouver Hospital and University of British Columbia.

A conference room is equipped with a video monitor and VCR machine so that the Daily Menopause Diary video could be watched by volunteers on site with a research assistant available to answer questions.

**Research personnel:**

The division of endocrinology provides a fertile research environment. Numerous investigators, technicians and researchers interact daily. A statistical consultant, [name], who is familiar with non-parametric tests and with evaluation of the Daily Menopause Diary is available and willing to work with us on this project.

[name], is skilled in the plethysmography assessment of forearm blood flow and will be responsible for the FBF studies and their analysis. Although [name] could potentially recruit women and serve as a research assistant, he is quite committed with other trials. He will draw the fasting blood samples and prepare and batch specimens for freezing and later analysis. He will also perform capillary glucose testing.

With the assistance of Drs. [name], [name] and [name], and [name], a skilled research administrator ([name]) will supervise data entry and will perform statistical analyses. (We will hire a skilled data entry firm to perform Daily Menopause Diary entry on site—we have taught several data entry people to put Daily Menopause Diary data into the computer with speed and accuracy.)

[name] will review the FBF and clinical data, will provide independent analysis of blood flow and clinical laboratory records. He will review and revise drafts of the paper and contribute to the overall conduct of the study by assisting with recruitment, evaluating the FBF data, and advising.

[name] will supervise every aspect of this project, especially data analysis. She will be responsible for negotiations with the sponsor concerning study conduct, finances, and publication of the results.

**Significance:**

Many women discontinued estrogen therapy abruptly after the results of the Women’s Health Initiative Study (WHI, 2002) were announced in July, 2002. Most are reluctant to re-start estrogen treatment. They need effective therapy for sleep-disturbing VMS. Preliminary work from our lab has shown in a blinded parallel group trial that was not placebo-controlled that medroxyprogesterone acetate is equally effective as conjugated equine estrogen in the control of VMS. Should Progesterone be shown to significantly improve VMS over placebo (an expected 30-40% placebo response) this would be a major therapeutic advance for women’s health. Progesterone may also be expected to improve vascular function because of previous studies and it is lipid neutral in several trials. Progesterone should not be as likely to concern women because it does not increase venous thromboembolism as estrogen does, is unlikely to cause strokes as it significantly lowers BP, and does not cause abnormal vaginal bleeding or migraine headaches.

If we are able to show improved forearm blood flow after three months of Progesterone therapy this observation would suggest it has important positive vascular effects. We have previously shown that endothelium-dependent forearm blood flow is improved by acute intra-arterial progesterone infusion in physiological luteal phase doses (Mather et al., 2000).

**Enrollment**

Introductory meeting (2 h)

Consent

Baseline Questionnaire

Quality of Life questionnaires:

MenQoL, SF-36

Weight, height, BP, HR, waist circumference

ECG

Video to explain the Daily Menopause Diary

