**Outcome measures:**

1. **Forearm blood flow** prospectively measured before and after three months of therapy.
2. **Vasomotor symptoms** prospectively recorded during the first month compared with changes in months one, two and three of the RDBPCT.
3. **Other hormone-related quality of life** measures on the Daily Menopause Diary, especially self worth, sleep, and energy.
4. **Changes in two published Quality of Life instruments** the Rand SF-36 and the Menopause-specific Quality of Life (MenQoL) questionnaires
5. **Lipid, BP and weight changes**—these will provide new and important therapy effects.

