**Methods:**

**Forearm blood flow**—this is a classical technique called venous occlusion plethysmography (Benjamin et al., 1995) in which forearm blood flow (FBF) is assessed using changes in a strain gauge at the widest forearm points bilaterally during periods of time in which hand arterial blood flow is occluded and venous arm flow is prevented compared with baseline control infusions (Mather et al., 2000).

A brachial arterial needle is in place for 2 hours during this procedure. However, this brachial arterial needle is much smaller than those used for patients in intensive care settings. Both the PI and the plethysmography technician have undergone this procedure, and women (n=27) in a prior study (Mather et al., 2000) found it acceptable.

Impaired endothelial function is a physiological risk factor for cardiovascular disease. Acetylcholine acts in conjunction with endogenously produced nitric oxide (NO) in order to increase blood flow, so the dose-response of forearm blood flow to acetylcholine measures endothelium-dependent control of blood flow.

Women will come to the lab fasting and having had no caffeine or food for 12 hours. Their BP, fasting capillary glucose and lipid profiles will be measured and they will be sent for an ECG. Over the two hour study, standard dose-escalating concentrations of acetylcholine and sodium nitroprusside are infused intrabrachially. Acetylcholine is to assess endothelium- or nitric oxide-dependent FBF changes and sodium nitroprusside is to assess endothelium independent FBF changes. The primary outcome measure is change in mean FBF during acetylcholine infusion adjusted for changes in the opposite, un-infused arm. All plethysmography measurements will be performed twice in each woman—at baseline and after three months’ blinded intervention.

**Daily Menopause Diary**--daily records will be obtained over four continuous months (one month of control data, and three on blinded therapy). Record-keeping using the diary will be taught using the videotape (Daily Perimenopause Diary 1995). Videos will be made available on loan during the study. Records will be reviewed twice during the baseline month to ensure good data collection.

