**One month after enrollment**

First Blood Flow test (venous occlusion plethysmography) (2 hours)

plethysmography test

copy completed Daily Menopause Diaries

start taking medication (progesterone or placebo)

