**About four months after enrollment**

Final Blood Flow test (venous occlusion plethysmography) (2.5 hours)

plethysmography test

copy completed Daily Menopause Diaries

return unused medication

final questionnaire

Quality of Life questionnaires:

MenQoL, SF-36

weight, BP, HR, waist circumference

Daily Menopause Diary

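### MenQoL, SF-36 and weight have their only pre-treatment value at enrollment, so their change scores span about four months for three months of treatment

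*Protocol*

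**What the plan says.** **Outcomes.** The Protocol, Outcome measures, includes "Changes in two published Quality of Life instruments" (SF-36 and MenQoL), and lists weight change together with lipids and BP. The Statistical analysis section says that all outcomes will be analysed as within-woman changes and compared by therapy.

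**Schedule (Appendix I, Study Flowchart).**
- Enrollment: MenQoL and SF-36, and "Weight, height, BP, HR, waist circumference".
- About three weeks after enrollment: fasting bloods and serum progesterone only.
- "One month after enrollment": first plethysmography test and copying of diaries, then women "start taking medication (progesterone or placebo". No questionnaire, weight or waist is listed.
- "About four months after enrollment": final plethysmography, MenQoL and SF-36, and "weight, BP, HR, waist circumference".

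**Methods, Forearm blood flow.** This section adds BP, capillary glucose, lipids and an ECG at the blood flow visits. It adds neither the questionnaires nor weight or waist.

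Waist circumference is measured but does not appear under Outcome measures.

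**The concern.** A change score is easiest to interpret when its baseline sits next to the start of treatment. For these measures the first value comes before the run-in month, so the score mixes a month of untreated observation and diary keeping with three months of drug or placebo. Two things follow. First, a baseline further from the final value usually correlates less with it, which adds noise to the comparison between arms. Second, the mean change within an arm includes whatever happened during the run-in, although the Outcome measures section presents the weight changes as therapy effects.

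The SAP cannot repair this. It can choose the estimator, but it cannot supply a value that the visit schedule does not collect.

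**Working it through.** **1. Interval.** The Design section gives one run-in month plus three randomised months, 1 + 3 = 4. The flowchart agrees: enrollment is month 0, first dose about month 1, final visit about month 4.
- Change score: 4 − 0 = about 4 months.
- Treatment: 4 − 1 = about 3 months.
- Untreated share of the interval: 1/4 = 25%. This describes the calendar and is not the size of an error.

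**2. Comparison with the other outcomes.**

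| Measure | Last scheduled value before treatment | Gap to first dose |
|---|---|---|
| MenQoL, SF-36 | Enrollment | about 1 month |
| Weight (and waist) | Enrollment | about 1 month |
| Lipids | Lab visit at about 3 weeks; Methods also has them at the blood flow visit | about a week or less |
| BP | Blood flow visit (Methods) | same visit |
| Forearm blood flow | Blood flow visit | same visit |
| Vasomotor symptoms and diary quality of life | Daily through the run-in | whole month up to first dose |

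**3. Bias between arms.** Write E, S and F for the values at enrollment, treatment start and final visit. Then F − E = (F − S) + (S − E). The second term comes before any treatment, so randomisation gives it the same expectation in both arms. The expected difference in F − E between arms therefore equals the expected difference in F − S, and there is no bias.

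**4. Precision.** With equal variance at both times, the variance of change is 2(1 − r) SD², where r is the baseline-to-final correlation. The protocol gives no r, so every value below is an assumption.
- r = 0.65 over 3 months: 2 × 0.35 = 0.70.
- r = 0.60 over 4 months: 2 × 0.40 = 0.80. Variance +14%, SD √(0.80/0.70) = 1.07, so +7%.
- r = 0.55 over 4 months: 2 × 0.45 = 0.90. Variance +29%, SD √(0.90/0.70) = 1.13, so +13%.
- Exponential decay, r₄ = r₃^(4/3): r₃ = 0.5 gives 0.397 and the SD goes from 1.000 to 1.098 (+10%); r₃ = 0.9 gives 0.869 and the SD goes from 0.447 to 0.512 (+15%).
- If r did not fall between three and four months, the loss would be zero.

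With baseline adjustment the residual variance is (1 − r²) SD²: 0.5775 at r = 0.65, 0.6400 at 0.60 (+11%) and 0.6975 at 0.55 (+21%). Adjustment reduces the loss but does not remove it.

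**5. Primary sample size.** The 50 per arm in the Statistical analysis section is for the vasomotor symptom score, whose baseline is the run-in month. It is not affected.

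**The case against.** **No planned test is biased.** This stands. The trial is placebo-controlled, and only the forearm blood flow null hypothesis also tests against baseline; that outcome has its baseline at the visit where treatment starts. The quality-of-life null hypothesis rests on the diary. SF-36, MenQoL and weight have no null hypothesis of their own. A reader might infer that the early baseline distorts the treatment effect; step 3 of the working shows that it does not.

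**Measurement conditions.** A reader might also infer that women were weighed fed at enrollment and fasted at the end, which would produce an apparent weight loss. Methods does say "Women will come to the lab fasting and having had no caffeine or food for 12 hours" for the blood flow visits. But the protocol does not state fasting status at enrollment, or when in the final visit weight is taken. A fed-to-fasted shift is only a possibility, and on average it would affect both arms alike.

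**The flowchart is not exhaustive.** Methods places BP, glucose, lipids and ECG at the blood flow visits, although the one-month entry in the flowchart lists none of them. Absence from that entry is therefore weaker evidence than it looks. However, no other section places the questionnaires, weight or waist there either.

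**Not every woman may have a blood flow study.** Methods says plethysmography is done twice in each woman, while the Statistical analysis section needs only about 30 recruits per arm for it. The remedy should therefore not depend on the blood flow study.

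**The size is assumed.** This stands. Applying the 0.58 SD effect at 50 per arm to a three-month change score would turn the exponential-decay case into a fall in power from about 83% to 72–75%. That effect size belongs to the vasomotor score, and the protocol sets no target for these outcomes, so the fall should not be quoted as a finding.

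**Conclusion.** The point holds as a matter of baseline timing in secondary outcomes. MenQoL, SF-36 and weight (and waist, which is not a listed outcome) are scheduled before treatment only at enrollment, about one month before the first dose. Their change scores span about four months for three months of treatment. This follows from the flowchart without further assumption, provided no unlisted measurement is taken at the one-month visit.

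There are two consequences, both modest. Precision is somewhat reduced, by an amount the documents do not allow one to calculate; the 7 to 15% increase in SD rests entirely on assumed correlations. And the mean change within an arm cannot be reported as a three-month therapy effect. The documents do not support a claim of bias between arms, of a demonstrated fasting artefact in weight, or of any effect on the primary outcome. This is a cheap improvement and does not threaten the trial's main result.

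**What to change.** In the flowchart entry for one month after enrollment, add MenQoL, SF-36, weight and waist before the first dose, for every woman, whether or not she has a blood flow study. Alternatively, move them there from the enrollment entry. State that these values are the baseline for change; if the enrollment values are kept, use them for description only.

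In the final-visit entry, take the same items under the same conditions and in the same order, before any blood flow study. State whether women are fasting when weighed, which also settles the open question about conditions.

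The cost is a flowchart amendment and some extra time, roughly 15 to 20 minutes by estimate, at a visit that already takes place. If the enrollment set is kept, women also complete the questionnaires once more; moving the set avoids that.

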**About 3 weeks after enrollment**

First Lab Visit (15 minutes)

fasting blood test (cholesterol, blood lipids)

fasting glucose

serum Progesterone level

**One month after enrollment**

First Blood Flow test (venous occlusion plethysmography) (2 hours)

plethysmography test

copy completed Daily Menopause Diaries

start taking medication (progesterone or placebo)

**About four months after enrollment**

Second Lab Visit (15 minutes)

fasting blood test (cholesterol, blood lipids)

serum Progesterone level

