**Participants:**

Menopausal women (final menstrual period one or more but less than 10 years before) without evidence of vascular disease (normal BP, without diabetes mellitus, normal cholesterol levels and non-smoker for at least a year, normal ECG) and with moderate VMS during the day and night. “Moderate VMS” are operationally defined for **daytime** as five flushes of a 1 intensity [on the 0-4 scale], 2-4 of a 2 intensity or 1-2 of a 3 intensity per week. Moderate VSM for **night** are defined as 1 flush of a 2 intensity or 2-3 of a 1 intensity per week.

Exclusion criteria:

Any menstruation in the preceding year.

A women who has had a hysterectomy without ovariectomy unless she is 60 years of age (and therefore could be confidently expected to be menopausal).

Use of ovarian hormone therapy (estrogen, progestin, progesterone or androgen) or SERM therapy (Raloxifene or Tamoxifen) in the preceding six months.

BMI over 35 or less than 20.

Mean of several pre-treatment BPs over 145/95 (supine, at rest, on no therapy).

History of abnormal cholesterol, abnormal fasting capillary glucose or a diagnosis of diabetes mellitus, any history suggestive of angina or having had an abnormal angiogram, ECG or exercise stress tests.

Finally, an abnormal baseline ECG consistent with ischemia or past infarction.

Randomization will be achieved using a random numbers table generated by computer with the code held by the dispensing pharmacy (Lancaster Medical).

All participants will be required to sign informed consent to a protocol approved by the University of British Columbia and Vancouver Hospital ethics review panels.

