**Statistical analysis:**

All baseline demographic information, Forearm Blood Flow (FBF) data and Daily Menopause Diary and laboratory information will be entered into a database. Data will be cleaned and analyzed before the therapy code is broken. Residuals will be examined for non-normality and, if necessary, will be analyzed using non-parametric statistics.

Numbers calculations:

Vasomotor symptoms are the primary outcome variable for the study, quantified as a composite score of number of VMS multiplied by the intensity during both the day and night (VMS Score). This method has been used by our laboratory in the past (Van Patten et al. 2002), and has also been used extensively by Loprinzi and his colleagues (Sloan et al. 2001). In short trials in about 1000 men and women, they suggest that 50 women per arm are necessary to provide 80% power to detect a 0.58 SD difference using the same standard two-sample, two-tailed t-test that we propose to use, with an alpha level of 0.05 (Sloan et al. 2001). This corresponds to a shift of 3 units of VMS Score per day.

The total sample size for this study is 125. That is made up of 50 women per arm, plus a 25% allowance for those who discontinue or who prove to be ineligible after enrollment.

Although there is no consensus on the clinically meaningful difference for vasomotor symptoms, 3 units of VMS score is a reasonable choice. Using re-sampling techniques from existing data, (68) show that this sample size is adequate to reveal the effects that they have found with a progestin and with non-hormonal agents such as vitamin E and anti-depressants. It is expected that there will be a placebo effect of 30-45 percent—this sample size allows for that expectation.

The forearm blood flow hypothesis requires approximately 25 women per arm. To reduce the numbers, all outcomes will be compared as changes *within* women (rather than cross-sectionally by group) over time, by therapy. Conservatively, we would need to recruit 30/arm to ensure 25 women per arm completing the three-month therapy study.

The mean FBF data (which we expect will be normally distributed) will be expressed as a within-woman change from baseline. The day and night VMS data will be analyzed separately as a product of intensity and the number. Where appropriate, analyses will use parametric methods. If necessary, non-parametric tests will be used for outcome variables that are non-normal. Changes within women over time by therapy will be compared.

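### Post-treatment serum progesterone, an assay of the study drug, is not kept out of the blinded database or away from the forearm blood flow review, so it can reveal the arm before the code is broken

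*Protocol*

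**What the plan says.** The Design section compares oral micronized progesterone with placebo. The flowchart in Appendix I measures serum progesterone at the first laboratory visit, before treatment, and again at the second laboratory visit about four months after enrollment ("serum Progesterone level").

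The Statistical analysis section says that "Daily Menopause Diary and laboratory information will be entered into a database", along with the baseline and FBF data. It then says: "Data will be cleaned and analyzed before the therapy code is broken". Examination of residuals, and a move to non-parametric methods if needed, follow in the same paragraph.

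Under Research personnel, one team member "will review the FBF and clinical data, will provide independent analysis of blood flow and clinical laboratory records". Another, the plethysmography technician, "is skilled in the plethysmography assessment of forearm blood flow and will be responsible for the FBF studies and their analysis". Of the technician the section also says: "He will draw the fasting blood samples and prepare and batch specimens for freezing and later analysis".

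The only blinding arrangement described for the randomization is in the Participants section: the list is computer-generated, "with the code held by the dispensing pharmacy".

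**The concern.** The assay measures the study drug itself. Participants are at least a year past their last period and have used no ovarian hormone therapy for six months, so a clear rise from the first sample to the second points towards the active arm. Holding the randomization list at the pharmacy does not help if a marker of treatment sits in the working database beside the outcomes.

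Cleaning and analysing before the code is broken is meant to ensure that decisions about queries, outliers, choice of test and acceptance of the FBF results are made without knowledge of treatment. If those making them can see post-treatment progesterone, the blinding is formal only. FBF matters here because the Methods section calls the change in mean FBF during acetylcholine the primary outcome measure, while the Statistical analysis section gives that status to vasomotor symptoms. The outcome whose reviewer also receives laboratory records is therefore not a minor one in this protocol.

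**Working it through.** The protocol gives no figure on this point to reproduce. The check is mainly a reading of the sections side by side.

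1. **Is there a post-treatment measurement of the study drug?** Yes, at the second laboratory visit (Appendix I). With the first visit, each completing woman has a before-and-after pair.
2. **Does it enter the blinded database?** Laboratory information does, and progesterone is not excepted (Statistical analysis). Progesterone is not named there either, so its inclusion follows from the general term.
3. **Does that database come before code break?** Yes. Cleaning and analysis both precede it (Statistical analysis).
4. **Can someone who judges FBF see laboratory results?** One team member has both sets of records (Research personnel). The record type is general and progesterone is not named.
5. **Does any text withhold, mask or delay the result?** None does. Batching and freezing for later analysis makes delay possible, but no section says that the assay waits for lock or code break.
6. **Is the result needed for a blinded analysis?** No. Serum progesterone appears in none of the Purposes, Null Hypotheses or Outcome measures.

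**How far could one value indicate the arm?** The protocol gives no progesterone levels, so this is an illustration under assumptions. Take two arms of equal size, normal distributions with equal variance, means *d* standard deviations apart, and a cut at the midpoint. The share of women assigned to the correct arm is Φ(*d*/2):

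| Assumed separation *d* (SD) | Φ(*d*/2) | Correctly assigned |
|---|---|---|
| 0.5 | Φ(0.25) | 60% |
| 1 | Φ(0.5) | 69% |
| 2 | Φ(1) | 84% |
| 3 | Φ(1.5) | 93% |
| 4 | Φ(2) | 98% |

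Guessing gives 50%. A large separation is plausible because the analyte is the drug. A long gap between last dose and sample, or non-adherence, would shrink it; the protocol does not fix the gap, and its sample-size allowance expects some women to discontinue. The inference is also asymmetric: a raised value suggests the active arm, while a low value may mean placebo or an active-arm woman who did not take her capsules.

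The sample size and power are not touched by any of this.

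**The case against.** The strongest case on the other side has four parts.

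- **The flow of results is inferred.** A reader might conclude that the protocol sends progesterone values to the FBF reviewer before code break. It does not say so. It speaks of laboratory information and clinical laboratory records in general and gives no release date, and freezing for later analysis means a result need not exist when FBF is reviewed. This stands, and the point is therefore stated as a risk. It does not remove the point, because the Statistical analysis section read literally puts laboratory data before code break and nothing makes an exception.
- **Custody of results is operational detail.** It may be set in a laboratory manual, data-management plan or SAP that is not shown. This has some force. However, the protocol itself promises analysis before code break, puts laboratory data in the analysed database, and gives one person both sets of records. The point rests on that combination, not on the absence of a manual.
- **Vasomotor symptom scores are largely protected.** Women record them daily, a hired firm enters them, and the second sample comes at about the end of recording, so the assay cannot influence what the women write. Choice of test is tied to examination of residuals. This stands. For this outcome only cleaning and analytic choices are exposed.
- **Subjectivity in FBF is not documented.** A reader might add that blood flow recordings need judgement in reading or exclusion. The protocol does not describe how recordings are read or excluded, so the room for an unblinded reviewer to influence FBF is unknown.

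**Conclusion.** The concern holds as a gap in safeguarding the blind. Followed as written, the protocol allows a result that can reveal the arm to be visible during data cleaning, choice of test and FBF review, and this undermines the blinded analysis it promises.

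This rests on two assumptions: endogenous progesterone is low in these women, and adherence and sampling time leave a detectable rise in the active arm. The proportion of women who would be identifiable depends on both and cannot be fixed from the document. Nor can the size or direction of any bias.

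A reader might infer that the blind is certain to be broken, or that the trial's results would be unreliable. The document supports neither: assay timing and levels by arm are unstated, the pharmacy-held code stays intact, and diary recording is unaffected. The change is worth making as a cheap improvement, because it closes the gap at no loss to any stated endpoint.

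**What to change.** Add a sentence to the Statistical analysis section, with a matching note at the second laboratory visit in Appendix I. It should say that post-randomisation serum progesterone results are kept out of the study database, and away from everyone who reads or reviews FBF, cleans data or runs analyses, until FBF readings and diary data are locked and the primary analysis has been run.

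Either of two routes will do: assay the already batched and frozen specimens after lock, or have the laboratory hold the results in a separate file and merge them then. Under Research personnel, make clear that the reviewer's laboratory records exclude post-randomisation progesterone until that time. Lipids are a stated outcome and can stay in the database.

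The cost is one sentence and, on the second route, a held results file. The downside is that exposure and adherence information from the assay becomes available only after lock.
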